**Beneficiary Registration**

All eligible children and women in the LHW´s catchment area will be registered before the first distribution by the LHWs as part of their routine activities. Thereafter, all newly pregnant women, lactating mothers and children 6-23 and 24-59 will be registered also as part of the normal LHWs duties.

After registration, the beneficiaries will receive a "programme ration card" that contains the registration number of the beneficiary (PLW/child) which will be used to receive the appropriate supplement.

At the moment of enrollment children´s height, weight and MUAC will be measured. Weight will be also measured on a monthly basis, while height will be measure at discharge time.

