**Study site**

This study will be conducted in 29 Union councils of districts Thatta and Sajawal of Sindh Province. The LHW catchment area of 29 targeted union councils of these districts will be in the intervention group, while remaining uncovered area of these union councils will be in control group. The UC wise details of LHWs, total population as well as covered and uncovered population are attached in annex I.

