All household with pregnant women, lactating mothers and children under five years of age will be eligible for baseline survey. LHW khandan register will be used to identify and select the eligible subjects in intervention clusters where available. A unique identification number will be assign to both children and mothers at the time of recruitment for the baseline survey. Social mapping approach (meeting with community elders, mothers, dais, community midwife, community/social workers etc.) will be used to identify the eligible subjects in control clusters. A list of eligible subjects will be prepared based on social mapping method and households with eligible subjects will be randomly selected for baseline survey.

Similarly all households with pregnant women, lactating mothers and children under five years of age at the time of endline will be eligible for endline cross sectional survey. Eligible subjects will be randomly selected from both intervention and control areas to see the overall impact of intervention on target population.

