**Recruitment of potential participants:**

Children 6-23 and 24-59 months of age and Pregnant or lactating mothers will be potentially eligible cohorts for inclusion in the study and will be identified through the baseline survey being done in the targeted union councils. Pregnant women will be enrolled during first and second trimester of pregnancy, children 6-23 months cohort during 6-18 months and children 24-59 months cohort during 24-54 months of age for minimum exposure of six months. A detailed recruitment form will be filled from each study participant. Detailed physical & anthropometric examination and sport Hb testing will also be done at the time of recruitment.

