**Plan of operations**

To ensure that various activities will be undertaken within the scheduled time for fieldwork, a comprehensive plan of operations will be planned as follows:

- Identification of resources
- Dialogue with the community elders / representatives
- Planning of field activities
- Questionnaire design and pre-testing
- Recruitment of field staff
- Training of field staff
- Mapping and selection of household
- Data collection & anthropometry measurements
- Data entry and cleaning
- Data analysis & reporting

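### The Protocol lists baseline participants by a different method in each arm, and the resulting selection difference can carry into the cluster randomised trial

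*Protocol*

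**What the plan says.** **Baseline frames.** In the Protocol section Sample size and design for Baseline and End line Surveys, the intervention frame is the register kept by the Lady Health Workers (LHWs): "LHW khandan register will be used to identify and select the eligible subjects in intervention clusters where available". For the other arm, social mapping with elders, mothers, birth attendants and community workers "will be used to identify the eligible subjects in control clusters". Random selection comes after that step: "A list of eligible subjects will be prepared based on social mapping method and households with eligible subjects will be randomly selected for baseline survey".

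**Endline frame.** The next paragraph of that section has eligible subjects drawn at random in both areas. It names neither the register nor social mapping.

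**Who is intervention and who is control.** For the surveys, Study site says: "The LHW catchment area of 29 targeted union councils of these districts will be in the intervention group". Survey controls, by contrast, live in those parts of the same places that LHWs do not serve: "while remaining uncovered area of these union councils will be in control group". For the CRT, Sample Size Estimation selects 12 of the 29 union councils (UCs), 6 per arm. It does not say whether control participants come from LHW-covered or uncovered parts of the control UCs.

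**CRT recruitment.** Under Recruitment of potential participants, the CRT cohorts "will be identified through the baseline survey being done in the targeted union councils".

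**The concern.** Random selection from a list represents only the people on that list. A register kept by health workers and a list built from community informants are likely to miss different households. If the missed households differ in stunting, the arms differ before any supplement is given.

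Randomising UCs balances the populations of the clusters in expectation. It does not protect against finding individuals within clusters by a method that depends on the arm. A team that chooses its frame by arm also has to know the arm when it identifies participants, which is a familiar route to recruitment bias in cluster trials.

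The double difference proposed under Methodology and Study Design is a partial safeguard for the surveys only. The CRT primary outcome, under Outcome Measures, is the risk of stunting in one group against the other and is not described as a double difference.

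**Working it through.** The Protocol gives no figure for frame coverage, so there is no plan figure to reproduce. The check has a textual part and an illustration based on assumptions.

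**1. Does the frame difference reach the CRT?** There are two cases.
- *CRT controls come from uncovered parts of the control UCs.* Intervention participants then come from the LHW register and controls from social mapping. The frame differs by arm, and so does LHW coverage itself.
- *CRT controls come from LHW-covered parts of the control UCs.* A register should exist there too, because Study Site and eligibility criteria says that all 29 UCs were chosen for LHW presence. One frame could then serve both arms. The difference would arise only if the words on control clusters were applied to the CRT control UCs.

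Study site and Sample Size Estimation do not settle which case applies.

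**2. Does the double difference cancel it in the surveys?** Let e be the error of a frame (listed minus population prevalence). The double difference retains (e_int,end − e_int,base) − (e_con,end − e_con,base). This is zero if each frame's error is the same at both rounds, which needs the same frames with stable coverage. The Protocol does not state this.

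**3. Size of one frame's error.** Let s be the share missed, L the prevalence in listed children and M that in missed children. The population value is (1 − s)L + sM, so e = s(L − M). Assumed ranges (none is in the Protocol): s = 0.10 to 0.30, L − M = 10 to 20 points in absolute size.
- Low: 0.10 × 10 = 1 point.
- High: 0.30 × 20 = 6 points.

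The between-arm bias is e_int − e_con. Two errors of equal size and sign cancel; errors of opposite sign add.

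**4. Yardstick.** Baseline stunting is 49% in the survey sample size section. A 10% relative reduction is 0.10 × 49 = 4.9 points; an absolute reduction is 10 points.

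**5. Effect on the false-positive rate in the CRT.** Inputs from Sample Size Estimation: 6 clusters per arm, m = 75 (top of the 70–75 range, children 6–23 months), intra-cluster correlation 0.02, two-sided α = 0.05. The 49% prevalence is stated for the surveys and assumed here for the CRT.
- Design effect: 1 + (75 − 1) × 0.02 = 2.48.
- Children per arm: 6 × 75 = 450.
- For a net frame difference b = 5 points and no true effect: SE = √[(0.49 × 0.51 + 0.44 × 0.56) × 2.48 / 450] = 0.0523, or 5.2 points.
- b/SE = 0.05 / 0.0523 = 0.96.

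| Net frame difference b (assumed) | False-positive rate, normal test | t-test, 10 df |
|---|---|---|
| 0 points | 0.05 | 0.05 |
| 2 points | 0.067 | 0.064 |
| 3 points | 0.088 | 0.081 |
| 5 points | 0.159 | 0.140 |
| 10 points | 0.488 | 0.415 |

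A net difference of 5 points would equal half of a 10-point effect or all of a 4.9-point effect. A larger sample would not remove it.

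**The case against.** **The frames follow from the survey design.** Control areas in the surveys are those without LHW cover, so no register is to be expected there. Differences in wealth, access or nutrition between covered and uncovered areas would remain even with a perfect common list. This stands: a common frame does not cure the non-random assignment of areas. It does not justify adding a second source of difference.

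**The register may be nearly complete.** The section on supplementary products delivery has LHWs visit every catchment household at least monthly. Nothing in the Protocol shows that the register omits a distinctive group. This also stands, and it is why no size or direction can be claimed.

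**Imbalance would be visible and adjustable.** Anthropometry is taken at CRT recruitment and quarterly, growth velocity is a secondary outcome, the surveys record a wealth index and LHW presence, and multivariate analysis is planned. A detailed survey protocol is also promised. These are partial remedies. Adjustment works on measured differences among people who were listed and cannot restore households that never were.

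**Two stronger readings are not supported.**
- A reader might infer that the frame difference certainly enters the randomised comparison. The text supports only that it can, because the CRT control area is undefined.
- A reader might infer that register coverage rises in the intervention arm during the programme, since under Beneficiary Registration all eligible children and women "will be registered before the first distribution by the LHWs as part of their routine activities". A rise from 75% to 95%, for example, would move the double difference by 0.20 × 10 to 20 = 2 to 4 points, with control coverage constant. But the Protocol does not say that ration registration updates the family register, nor that the register is used again at endline. This is an assumption and is not relied on here.

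**Conclusion.** The point holds as a design weakness. The arm-specific baseline frames, the use of that survey to identify the CRT cohorts, and the lack of a named endline frame are all in the text. What an arm-dependent list leaves out is not repaired by random selection from that list or by randomisation of UCs, and it is repaired by differencing only under conditions that the Protocol does not state.

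Its size is unknown. The 1–6 points describe one arm's error under assumed coverage and assumed stunting gaps. The net bias could be smaller, zero or of either sign. At the upper part of that range it would match or exceed the 4.9-point reading of the target. Entry into the CRT is conditional on where control participants are drawn. The Protocol should be changed on this point because the remedy is cheap and an analysis plan cannot supply it later.

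**What to change.** 1. In Sample size and design for Baseline and End line Surveys, prescribe the same household listing method in intervention and control clusters at both baseline and endline. Draw households at random from that list, and keep the LHW register only as a cross-check on completeness.
2. In Recruitment of potential participants, state whether CRT controls come from LHW-covered or uncovered parts of the control UCs, and reconcile this with Study site and the CRT Sample Size Estimation.
3. In the same place, list and recruit CRT participants in both arms from the common frame, where feasible before the UC allocation is revealed to field teams.

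The cost is some extra listing time in intervention clusters. Teams already list eligible subjects in control clusters, and Plan of operations already includes "Mapping and selection of household". The rest is Protocol wording. The change removes the frame difference, not the separate non-random difference between covered and uncovered areas in the surveys.

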**Outcome Indicators for the survey**

| **Topics** | **Key variables** |
| --- | --- |
| Basic demographic characteristic of the household | Sex of the household head and children being assessed  Education level of the head of household and the spouse  Household size  Occupation of respondent and household head |
| Socio-economic characteristics of the household | Household wealth index  Type of the dwelling  Household residence status  Access to land and animals ownership |
| Household access to health services, water and sanitation | Distance to the nearest health facility  Main constraints to access health services  Presence of LHW  Main source of drinking water  Type of sanitation facility |
| Women´s care capacity | Women´s education level  Women´s reproductive history  Antenatal / postnatal care / immunization during pregnancy  Knowledge about vitamins , Anemia, iodized salt |
| Women’s physical examination and anthropometry | Physical examination for signs of anemia  Hemoglobin test results  Anthropometry |
| Household and children feeding practices | Prevalence of:   - exclusive breastfeeding - children ever breastfed - timely introduction of solid and semi-solids - early introduction of liquids - adequate dietary diversity - minimum meal frequency - minimum acceptable diet - consumption of iron-rich or fortified foods   Household food consumption and diet diversity  Consumption of iron-rich or fortified foods  Consumption of iron and folic acid supplements  Household coping strategies  Food insecurity |
| Children health status | Prevalence of reported illness (Fever, Diarrhea and ARI)in the past two weeks  Treatment type  Type of care provider  Immunization status |
| Child physical examination and anthropometry | Physical examination for signs of anemia  Hemoglobin test results  Anthropometry |
| Exposure to other interventions | Existence, type and coverage of other interventions related to food security, health and nutrition  Percentage of households, women and children already benefiting from interventions |

**Operational Survey Procedures**

**Development of Survey Protocol and Manuals:**

At the outset a detailed survey protocol will be developed in the first phase of survey. The protocol will cover both component of project.

**Development of Instruments:**

Data collection instruments will be developed in English and will include information on demographics; socioeconomic status; knowledge, attitudes and practices (KAP) and information related to the maternal and child health, nutrition status, food consumption & feeding practices and food insecurity. Similarly a recruitment form for the eligible children and PLW will also be developed. The project team will also develop the quarterly surveillance form through which the data will be collected during the quarterly surveillance rounds. The questionnaires will be translated into Sindhi and then back translated into English to assess whether the essence of the questions had been captured.

**Team Structure for Quantitative Component**

The project involves both major components which are data collection at household level, Anthropometric measurements and haemoglobin testing. Following is the team structure that has been proposed for the impact assessment study.

[figure not shown]

All project team members will be selected locally from Thatta and Sajawal. Female data collectors will collect the required information from the women and will conduct anthropometric measurements and Hb testing of the selected children and women. A male team leader will lead his team comprised of four female data collectors.

**Training**

Three trainings one for baseline, one for end line and one for the CRT will be done during the course of the project. Five days intensive training workshop will be organized for all local staff. This training workshop will be organized in four phases:

- One day combined session for all field staff (team leaders, data collectors and community nursing team) on background, objectives, methodology and timelines of the study.
- Two days session for data collectors on assessments of project and anthropometry
- One day joint mock field activity for the conceptual clarity on study procedures
- One day, feedback on the field visit and activities and finalization of teams

**Proposed Training scheme**

| **All participants** | **Team Leaders** | **Data collectors** |
| --- | --- | --- |
| General Introduction and Survey Methodology | Supervision skills  Quality assurance  Sampling methodology  Documentation  Reporting | Interviewing skills  Consent procedures  Q by Q Instrument review  Sampling Methodology  Operational Procedures  Field Procedures, Daily documentation /log sheets  Physical examination, Hemoglobin testing  Anthropometry  Field Practice |

The training agenda will cover the following points:

- Purpose of the project
- Roles and responsibilities
- Introduction to two stage cluster sampling technique and related issues
- Interviewing techniques
  - Selection of place for the interview
  - Consent taking and describing the process and the project
  - Attendance of others during the interviews / gaining community support
  - Probing/Rewording
  - Be prepared for any answer
  - Listen to the respondents
  - Answering respondents objections
  - Stress benefits of the survey
- Definition and technical aspects of different methodologies and terminologies
- Selection of procedures and use of interview tools
- Explanation of the questionnaires, question by question practice through simulated interview
- Field practices (mock interviews)
  - Critique of field practice
- Administrative procedures
- Anthropometry technique
- Clinical examination for anemia +Hb
- How to handle refusals
- Field quality checks
- Questionnaire review for completeness
- Quality Control and Quality Assurance
- Confidentiality and ethical issues

**Field Testing:**

Field testing will be performed on all aspects of the project. The questionnaire will be translated into the local language and tested. Field testing is useful to estimate the amount of time it will take to complete the interview and to identify any potential problems with the survey instruments and protocol. The field testing will be undertaken in conditions similar to the field within districts Thatta and Sajawal to simulate the actual data collection. Questionnaire validation and other community-level training activities will take place in areas different from those selected for the project. Following the field test, all project teams should convene and discuss the experience and modifications can be made, if necessary, to the protocol and data collection tools.

**Liaison with the Local Partner:**

Consultative meetings will be done with all relevant stake holders before the finalization of project protocol and methodology.

**Data Collection & Monitoring**

The data will be collected by trained female data collectors at household level; they will be allocated a set of households on daily basis. The whole activity of the data collection will be supervised and monitored by a team leader and field supervisor who will be trained to supervise this task. Morning meeting will be being conducted by the team leader/supervisor every day. An informed consent will be taken from the respondent in every household from where the data is collected. After field work data collection teams will return to the office for rechecking of forms before handing it over to concerned supervisor. The team leader will check the entire filled questionnaire for completeness before hand over to field supervisor. Field supervisor and desk editor will review the filled questionnaire for errors and inconsistencies. In case any errors and inconsistencies are identified the forms will be given back to the data collectors for correction from the field. After review and coding, all forms will be handover to DMU for data entry.

**Proposed Monitoring & Supervision Checks at Different Level:**

Effective supervision and monitoring is key to the success of any project. The project activities will be regularly monitored by various staff; the team leader will monitor the activities of every data collector. There will be several cross checking level during the assessments to ensure quality of data collected. Suggested checks during the survey are schematically presented in the figure below:

**At the end of each household**, the team leader should check if;

- Questionnaire headings such as name, date and household number are properly filled in
- All the questions has been answered
- Age has been correctly estimated and proper source is used (Birth certificate, local event calendar, vaccination card or any other official document verifying age)
- Weight and height has been properly entered
  - No rounding off of these variables.
  - Skip pattern has been respected

**Before leaving the area**, the team leader should check;

- The number of questionnaires corresponding to the number of households
- Any missing and absent subject should be checked
- Ensure all the absent subjects are visited again at the end of day

**At study office,** supervisors should check the selection of household, refusals, and check all questionnaires for completeness. In addition randomly select 5 % of households for revisits to cross-check the responses and the measurements.

**B. Impact Assessment of the Project:**

**Nested Cluster Randomized Controlled Trial**

During intervention delivery, a randomized controlled trial will also be conducted on a sub-set of targeted subjects for further robustness and to get the in-depth evidence about the impact of interventions on health and nutrition outcomes.

The Aga Khan University proposes an embedded Cluster Randomized Controlled Trial for more robust evaluation of the intervention being carried out by WFP. This CRT will be done at union council level to assess the acceptability, feasibility and effectiveness of food based interventions to prevent stunting among children in community settings. The project will utilize the window of opportunity (1000 days from conception to 2 years) for addressing stunting in children under-five years. Therefore project will recruit three types of cohorts in the study i.e. children 6-23 months, children 24-59 months and pregnant women to follow the newborns who delivered from recruited pregnant women.

**Methodology for Cluster Randomized Controlled Trial**

**Sample Size Estimation:**

A union council has been taken as the cluster for the estimation of sample size for RCT. The following three sample sizes were calculated to detect a range of differences in nutritional status for all study participants;

1. Pregnant and Lactating Women: To calculate sample size for PLW, we aimed to achieve a 25% difference in the prevalence of low birthweight. With a power of 0.80 and a statistical significance of 0.05, we calculated that a sample size of 160-170 per cluster would be sufficient for analyzing the reduction in low birthweight. A total of 2,000 PLW will be enrolled in the trial.
2. Children 6-23 months: Sample size for children aged 6-23 months was calculated to detect a 10% difference in risk reduction in stunting among the intervention group compared to the control group. A sample size of 70-75 children per cluster was estimated with a statistical significance of 0.05, power of 0.80, and an intra-cluster correlation of 0.02. A total of 900 children, 6-23 months old will be enrolled in the trial.
3. Children 24-59 months: To detect a 10% difference in risk reduction in stunting among the intervention group compared to the control group, a sample size of 90-95 children per cluster was drawn, with a statistical significance of 0.05, power of 0.80, and an intracluster correlation of 0.02. A total of 1100 children aged 24-59 months will be enrolled in the trial.

The total sample size will be taken from 12 union councils which will be randomly selected from the list of 29 union councils, 6 union councils for intervention group and 6 union councils for control group.

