**Sample size and design for Baseline and End line Surveys**

Clearly it would be impossible to conduct an in-depth evaluation of all population in the community based nutrition program. However, the assessment must be robust, scientifically valid and plausible within existing time frames. Therefore a representative sample size has been calculated separately for both baseline & endline surveys and embedded Randomized control trial. Details of both estimations are as under:

Below mentioned formula for sample size estimation for baseline and endline cross sectional surveys were used from MI & CDC manual [6] to calculate the sample size. Prevalence of stunting (49% Sindh) from NNS 2011, 80% power to detect 10% reduction in prevalence of stunting during the three-year implementation of the Stunting Prevention Programme with a significance level of 0.05 was considered for sample size estimation.

[figure not shown]

Assumptions:

- p1 is stunting rate at baseline without intervention at baseline survey =49%
- p2 is estimated stunting rate after intervention at end line survey
- DEFF : The estimated design effect = 1.5
- α : Level of significance (“alpha”), usually 0.05 or 5% (corresponds with 95% confidence interval)
- 1- β: Power, usually 0.8 (80%) Assumed 10% reduction in stunting

For estimating impact of the interventions each group will require 3200 participants. To account for dropouts and data errors, the sample size will increased by 10% giving a new total of 7040 study participants (3520 participants per group). Information will be collected from 4,200 households at baseline and at endline. The study participants from selected households will be pregnant women, lactating women and children under five years. Two stage cluster sampling technique will be used. LHW catchment areas of 29 UCs will be treated as a cluster for intervention group and control group.

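### The low-birth-weight sample size states neither an ICC nor a control rate, so its 80% power cannot be verified, and the 2,000 women are not clearly all pregnant at enrolment

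*Protocol*

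**What the plan says.** The Sample Size Estimation section of the cluster trial sets the unit for all three cohorts: "A union council has been taken as the cluster for the estimation of sample size for RCT". There are "6 union councils for intervention group and 6 union councils for control group".

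For pregnant and lactating women (PLW), item 1 states the target, "we aimed to achieve a 25% difference in the prevalence of low birthweight", and the error rates, "With a power of 0.80 and a statistical significance of 0.05". It concludes: "we calculated that a sample size of 160-170 per cluster would be sufficient for analyzing the reduction in low birthweight". The total follows: "A total of 2,000 PLW will be enrolled in the trial". No ICC and no control LBW rate appear. Items 2 and 3, on stunting in the two child cohorts, each state an ICC of 0.02.

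On who is enrolled, the Nested Cluster Randomized Controlled Trial section describes the maternal cohort as pregnant women whose newborns are followed. The Recruitment of potential participants section makes both pregnant and lactating mothers eligible, restricts pregnant women to the first two trimesters, and says that participants "will be identified through the baseline survey being done in the targeted union councils". The survey section sets the size of that survey: "Information will be collected from 4,200 households at baseline and at endline".

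**The concern.** A per-cluster size for a cluster-randomised comparison means little without an ICC, and a relative reduction in a proportion cannot be sized without a control rate. Item 1 lacks both. With about 167 women per union council, even a small ICC inflates the variance considerably, so it matters whether clustering was allowed for.

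Separately, if some of the 2,000 have already delivered when they enter, the number of births behind the LBW comparison is smaller than the number enrolled.

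LBW is a named objective of the evaluation and the only maternal or birth outcome that is sized. A null LBW result from a comparison advertised at 80% power could be read as failure of the programme when the comparison was in fact weak.

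**Working it through.** **Inputs from the protocol.** Alpha 0.05, power 0.80, a 25% difference, 6 against 6 union councils, 160–170 women per council, 2,000 in total.

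**Assumptions.** Two-sided test. The 25% is read as relative, so p2 = 0.75 × p1; an absolute difference of 25 points would need only about 36–58 women per arm before clustering at control rates of 30–50%, far from the stated size. The control rate p1 and the ICC are varied because the protocol gives neither. All 2,000 women are taken to contribute a birth.

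**Step 1: internal arithmetic.** 2,000 / 12 = 166.7 per council, inside 160–170, or 1,000 per arm. The stated range corresponds to 960–1,020 per arm. There is no slip here.

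**Step 2: which inputs return the stated size without clustering?** With

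n per arm = [1.96 √(2p̄(1−p̄)) + 0.8416 √(p1(1−p1) + p2(1−p2))]² / (p1−p2)², where p̄ = (p1+p2)/2:

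- p1 = 0.185: 995 per arm, 166 per council
- p1 = 0.19: 964 per arm, 161 per council
- p1 = 0.20: 906 per arm, 151 per council, which is below the stated range

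So the size is reproduced with no ICC at a control rate of about 18–19%. A one-sided test reproduces it at about 15% (1,002 per arm).

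**Step 3: design effect.** DEFF = 1 + (166.7 − 1) × ICC.

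| ICC | DEFF | Effective n per arm (1,000/DEFF) | Control LBW at which 1,000 per arm gives 80% power |
|---|---|---|---|
| 0 | 1.00 | 1,000 | about 18% |
| 0.005 | 1.83 | 547 | about 30% |
| 0.01 | 2.66 | 376 | about 39% |
| 0.02 | 4.31 | 232 | about 52% |

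**Step 4: power with 1,000 per arm.**

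| ICC | Control LBW 20% | 25% | 30% |
|---|---|---|---|
| 0.005 | 59% | 71% | 81% |
| 0.01 | 44% | 55% | 65% |
| 0.02 | 29% | 37% | 45% |

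**Step 5: can larger clusters help at ICC 0.02?** As cluster size grows, effective n per arm approaches 6 / 0.02 = 300. The unclustered need is 295 at p1 = 0.45 and 686 at p1 = 0.25. With six councils per arm, 80% power is therefore out of reach at any cluster size unless control LBW is about 45% or more.

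**Step 6: survey households.** If the 4,200 households were spread evenly over the 29 councils, the 12 trial councils would hold 4,200 × 12 / 29 = 1,738. Enrolling 2,000 women from these alone would take 2,000 / 1,738 = 1.15 women per household. The even spread is an assumption; the protocol gives no allocation per council.

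**The case against.** The strongest reply is that silence about the ICC does not show that clustering was ignored. A reader might infer that no ICC was applied and that the study lacks the power it claims. The protocol does not establish either. With the control rate missing, an ICC near 0.005 and LBW near 30% also return the stated size and give 81% power. ICCs are specific to an outcome, and the 0.02 is stated for stunting; carrying it over to LBW is an assumption. This stands. It limits the conclusion to a power that cannot be verified and is sensitive to the ICC.

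A reader might also infer that a known share of the 2,000 will be lactating. The protocol gives no such split. PLW is the programme's label for women supplemented through pregnancy and for six months after birth, so the total may mean women enrolled while pregnant and followed into lactation. That is a fair reading, but the recruitment section admits lactating mothers as an alternative to pregnant ones and does not settle the question.

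Nor does the household figure show that recruitment is impossible. The survey section describes lists of eligible subjects, from health worker registers where available and from social mapping in control clusters, drawn up before households are sampled. Identification through the survey may include that step. The programme also registers newly pregnant women on a continuing basis.

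Finally, LBW is a secondary outcome; stunting is primary.

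**Conclusion.** The point holds in limited form. The 80% power for LBW cannot be checked, because the two inputs that determine it are absent. The stated size fits an unclustered calculation at a control rate of about 18–19%. It fits the ICC used for the neighbouring cohorts only if about half of control newborns have low birth weight. Over assumed control rates of 20–30%, power runs from 29% to 81% across ICCs of 0.005–0.02 and reaches 80% only at the most favourable corner. These figures assume a relative 25% reduction, a two-sided test, equal clusters, a birth outcome from every woman, and a normal approximation, which is generous with 12 clusters.

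The composition of the 2,000 is an unresolved conflict between sections, and any woman already lactating at entry lowers the power further. The recruitment source is a minor matter of wording. Because LBW is secondary, the change should be made but does not threaten the primary comparison.

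**What to change.** In item 1 of the Sample Size Estimation section:

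- State the assumed control LBW rate, the ICC with its basis, and whether the 25% is relative. Restate the power with the design effect for six clusters per arm, preferably over a small range of ICCs.
- State the 2,000 as women pregnant at enrolment. Restrict the LBW analysis to them and report any women enrolled while lactating separately. Align the nested-trial and recruitment sections with this.

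In the Recruitment of potential participants section, say that the trial recruits from the full lists of eligible subjects described for the baseline survey, and not only from the sampled households.

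The cost is wording and the use of lists already planned. The stated power for LBW will probably fall, and a null result should then be reported with its confidence interval and not as evidence of no effect.
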